### Outcomes

#### Primary feasibility outcomes

Recruitment and completion will be measured in the numbers of participants enrolling and completing all study visits;Supplementation compliance will be measured both by capsule counting (participants returning packaging and untaken supplements) and the measurement of ergothioneine in plasma by HPLC at baseline, 6 weeks and 12 weeks.

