### Study objectives

To assess feasibility of recruiting and supplementing people with metabolic syndrome with ergothioneine for 12 weeks.To investigate if any changes in serum markers of oxidative stress (lipid peroxidation), inflammation and liver function can be observed in response to ergothioneine supplementation.To examine if any changes in oxidative and inflammatory stress in blood immune cells can be observed in response to ergothioneine supplementation.To assess if there are any changes in metabolic syndrome risk factors or in the serum metabolome in response to ergothioneine supplementation.To use the data to determine dose of ergothioneine and participant numbers needed to inform a primary outcome for a definitive randomised controlled trial.

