### Sample size

As a consequence of a complete lack of data on which to base either a primary outcome or a formal power calculation, and in line with the appropriate CONSORT extension [24], a primary aim of this pilot trial is to generate the data to inform the design of a definitive trial. The decision to recruit a total 108 participants was a pragmatic one based both on statistical arguments for sample size in pilot/feasibly trials and the need to balance maximizing precision while minimizing the impacts of size on resources, time and costs [25, 26]. With a goal of 90 measured participants (30 per group), we aim to recruit 108 participants to allow for 20% drop out per group. This number is in line with previous calculations suggesting between 25 and 35 participants per group will typically provide sufficient power to determine the effect size for a sample size calculation without being wasteful of resources [25–27].

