### Recruitment

We will recruit participants in several ways. People with metabolic syndrome who participated in a previous study in our School (the PATHWAY-27 study [28]), and consented to be contacted again for other research studies, will be contacted by phone or email to ask if they are interested in taking part in another intervention trial. We will also advertise the study broadly through conventional and social media and via multiple relevant charities (e.g. British Heart Foundation and Diabetes UK). We aim to achieve Health Research Authority approval, which will also permit recruitment through general practitioners’ offices. Based on experience with the PATHWAY-27 study [28], we anticipate recruitment and running of the trial to take 2 years. In the context of unforeseen risk events such as COVID19 or low recruitment rates, given our block design this time can be extended.

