### Assignment of interventions

#### Allocation

While enrolment will be done by the study team, the randomisation schedule and allocation will be carried out by a collaborator who will not be involved in any other part of this trial and who will also be blinded to the dose allocation (Interventions ‘1’, ‘2’ or ‘3’; Fig. 1) designated by the manufacturer and provided in a sealed envelope. Randomisation and group allocation will be done based on predefined random allocation lists using simple stratification for sex (one each for males and females), with a block size of 6 and allocation list of 2:2:2; aiming to recruit 108 participants for *n* = 36 in each group.

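### The recruitment part of the primary feasibility outcome is a bare enrolment count over an extendable period, so it cannot by itself show that recruitment is too slow

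*Protocol article*

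**What the plan says.** All references are to the protocol article.

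- **Study objectives.** The first objective is "To assess feasibility of recruiting and supplementing people with metabolic syndrome with ergothioneine for 12 weeks".
- **Primary feasibility outcomes.** "Recruitment and completion will be measured in the numbers of participants enrolling and completing all study visits". The text gives no time base for enrolment. Compliance, by capsule count and plasma ergothioneine, is listed as a second feasibility outcome.
- **Recruitment.** Drawing on an earlier study, "we anticipate recruitment and running of the trial to take 2 years". The next sentence adds: "In the context of unforeseen risk events such as COVID19 or low recruitment rates, given our block design this time can be extended". No maximum is given.
- **Sample size.** "With a goal of 90 measured participants (30 per group), we aim to recruit 108 participants to allow for 20% drop out per group".
- **Discussion.** The authors expect that the many exclusion criteria may lengthen the recruitment period.

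**The concern.** Feasibility of recruiting is half of the first objective. The article measures it by how many people enrol, yet slow recruitment is itself a stated reason for recruiting longer. The event the outcome should detect thus sets off the rule that hides it. The Discussion also expects difficulty to appear as elapsed time, which the outcome does not record.

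The pilot exists to inform a definitive trial. To plan the length of that trial and its number of sites, the team needs a recruitment rate and a screening yield. A final count of 108 supplies neither.

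**Working it through.** **Inputs from the article.** Target 108 recruited; goal 90 measured (30 in each of 3 groups); 20% dropout; anticipated duration 2 years (24 months); 12 weeks of supplementation per participant. True monthly rates and the longest possible extension are not given, so those used below are assumptions.

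**1. The plan's own figure.** 30 × 1.20 = 36 per group, and 36 × 3 = 108. The stated target is reproduced.

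**2. Implied recruitment rate.** Rate = 108 / months.
- All 24 months used: 108 / 24 = 4.5 per month.
- Last 12 weeks kept for follow-up: 12 weeks = 84 days / 30.44 = 2.76 months, so 108 / (24 − 2.76) = 108 / 21.24 = about 5.1 per month.

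**3. What the final count can tell apart.** The same 108 results from:

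| Months | Rate per month |
|---|---|
| 24 | 4.5 |
| 36 | 3.0 |
| 48 | 2.25 |
| 60 | 1.8 |

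The enrolled number is the same in every row.

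**4. Chance of reaching 108.** Treat enrolment as Poisson with mean rate × months and compute P(X ≥ 108). Rates and extended windows are assumed.

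| True rate per month | 24 months | 36 months | 48 months | 60 months |
|---|---|---|---|---|
| 2 | <0.001 | <0.001 | 0.12 | 0.87 |
| 3 | <0.001 | 0.51 | 0.999 | >0.999 |
| 4 | 0.12 | 0.999 | >0.999 | >0.999 |

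At a fixed 24 months the count separates these rates from the plan's 4.5. With a window that can stretch, it does so less and less.

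**5. Would a rate at 2 years be informative?** The exact Poisson 95% CI for x participants in T months runs from χ²(0.025; 2x) / 2T to χ²(0.975; 2x + 2) / 2T.
- 54 by 24 months: 54 / 24 = 2.25 per month, CI 1.69 to 2.94, which excludes 4.5.
- 108 by 24 months: 4.5 per month, CI 3.69 to 5.43.

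A site running at half the implied pace would be recognised clearly.

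**6. Completion.** The two counts give a proportion. Exact (Clopper-Pearson) 95% CIs:
- 54/108 = 50%, CI 40% to 60%
- 86/108 = 79.6%, CI 71% to 87%
- 90/108 = 83.3%, CI 75% to 90%

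If true completion were 70%, the chance of at least 90 completers among 108 would be 0.001, so this component can fail however long enrolment took.

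The Sample size section does carry two references that disagree. The goal of 90 is 90/108 = 83.3%, while 20% dropout leaves 108 × 0.80 = 86.4. A result of 87 completers would pass one and miss the other.

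**The case against.** A reader might go further and infer that the pilot cannot show infeasibility at all, or that the first objective can never be answered no. The article does not support that. The objective covers supplementing as well as recruiting. Numbers enrolling and numbers completing are both reported, so the first is the denominator of the second. The Sample size section gives a reference for completion, and the Statistical methods section promises 95% confidence intervals. Compliance is a separate feasibility outcome. Poor completion or compliance would show infeasibility whatever the recruitment time. All of this stands, and it confines the point to recruitment.

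It can also be said that nothing in the article equates reaching 108 with success. Extension is allowed, not required, and it protects the numbers needed for the pilot's other aims. Actual duration can be set against the expected 2 years. This stands in part: an informal comparison is possible, but duration is not part of the defined outcome, and the article fixes no point at which the comparison is made.

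Finally, rate definitions and progression criteria are often left to a full protocol, which is not shown. Their absence is therefore no finding here. The point rests on what the article does state: a metric and an extension rule that work against each other.

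**Conclusion.** The concern holds for the recruitment component only. As defined, the enrolled count cannot by itself show that recruitment is too slow, because the period may be lengthened, without a stated limit, when recruitment is low. A site recruiting at 2.25 per month, half the implied 4.5, would be expected to post the same 108 after 48 months.

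The identity of the counts in step 3 needs no assumption beyond the article's own target. The probabilities in step 4 rest on assumed constant rates, Poisson enrolment and illustrative windows of up to 60 months. Completion and compliance are unaffected. For completion, the only repair needed is to choose between the two references.

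**What to change.** Amend the Primary feasibility outcomes section as follows.

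1. **Recruitment.** Define it as participants randomised per month, with a 95% CI, over the originally planned 2-year period. State the reference and its window together: 4.5 per month over 24 months, or about 5.1 if the last 12 weeks are kept for follow-up.
2. **Extension.** Keep the option for the other aims. If it is used, report the rate at the 2-year point as the recruitment feasibility result and give the later recruitment separately.
3. **Screening yield.** Report the proportions screened, eligible and randomised.
4. **Completion.** Report the proportion of those randomised who attend all visits, with a 95% CI, against one named reference. The goal of 90 implies 83.3%; a benchmark of 80% would accept about 86 completers, short of that goal. The intervals for 86 and for 90 completers both contain 80% and 83.3%, so say in advance whether the point estimate or a confidence limit is compared with the reference.

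The cost is mainly wording. Screening is already done online (Consent), the eligibility questionnaire is collected digitally (Data management, confidentiality and access), and screening IDs are matched to randomisation IDs (Blinding). Sample size, visits and interventions do not change. The one small downside is that the pilot can now miss its own recruitment expectation.

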#### Secondary exploratory outcomes

At baseline, 6 weeks and 12 weeks, we will measure:A primary serum marker of oxidative stress (specifically, lipid peroxidation), malondialdehyde (MDA), which we hypothesize could be the future primary outcome for powering a future definitive trial;Serum markers of inflammation (tumour necrosis factor-alpha (TNF-α) protein, nuclear factor erythroid 2-related factor 2 (Nrf2) protein, c-reactive protein (CRP), soluble CD36, NADPH oxidase 4 (NOX4) mRNA) and liver function (ALT);The activation status of blood platelets, platelet reactive oxygen species (ROS) generation and inflammatory platelet-leukocyte aggregates;Metabolic syndrome risk factors: body weight (for BMI calculation, height will be measured at baseline only) and waist circumference, blood pressure, triacylglyceride (TAG), high-density lipoprotein (HDL) cholesterol and fasting glucose;Serum metabolites.

### Participant timeline

The participant timeline and schedule of the intervention is outlined in Table 1 in accordance with SPIRIT guidelines.

**Table 1 Tab1:**
[figure not shown]
Participant timeline from initial screening to end of study

^a^*t*_1_, baseline; *t*_2_, 6 weeks, *t*_3_ 12 weeks

### Sample size

As a consequence of a complete lack of data on which to base either a primary outcome or a formal power calculation, and in line with the appropriate CONSORT extension [24], a primary aim of this pilot trial is to generate the data to inform the design of a definitive trial. The decision to recruit a total 108 participants was a pragmatic one based both on statistical arguments for sample size in pilot/feasibly trials and the need to balance maximizing precision while minimizing the impacts of size on resources, time and costs [25, 26]. With a goal of 90 measured participants (30 per group), we aim to recruit 108 participants to allow for 20% drop out per group. This number is in line with previous calculations suggesting between 25 and 35 participants per group will typically provide sufficient power to determine the effect size for a sample size calculation without being wasteful of resources [25–27].

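### Recruiting 108 with 20% dropout leaves about 86 measured participants (28.8 per group), not the stated 90 (30 per group); the effect is small and one sentence corrects it

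*Protocol article*

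**What the plan says.** The Sample size section of the protocol article links three figures in one sentence: "With a goal of 90 measured participants (30 per group), we aim to recruit 108 participants to allow for 20% drop out per group". Under Assignment of interventions, the Allocation section repeats the recruitment total and gives the split by arm, "aiming to recruit 108 participants for *n* = 36 in each group", using blocks of 6 with equal allocation.

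The Sample size section also sets the context. It reports a "complete lack of data on which to base either a primary outcome or a formal power calculation" and calls the choice of 108 pragmatic. It then supports the group size by citing earlier work according to which "between 25 and 35 participants per group will typically provide sufficient power to determine the effect size".

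**The concern.** Dropout is ordinarily expressed as a share of those enrolled. Read that way, the recruitment total does not deliver the stated number measured at the stated dropout rate, so at least one of the three figures is wrong.

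What is at stake is the accuracy of a planning statement. A reader cannot tell whether the trial is meant to tolerate 20% loss or to end with 90 measured participants, because 108 recruits cannot do both.

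**Working it through.** **Inputs.** From Sample size: 90 measured in total, 30 per group; 108 recruited; 20% dropout per group; cited adequate range 25 to 35 per group. From Allocation: 36 recruited per group, block size 6, equal allocation.

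**Reproducing the plan's figure.** Adding 20% to the target gives 90 × 1.20 = 108 in total and 30 × 1.20 = 36 per group. Both match the protocol exactly.

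**Expected number measured at the stated dropout rate**, recruited × (1 − dropout):
- Total: 108 × 0.80 = 86.4, which is 90 − 86.4 = 3.6 short.
- Per group: 36 × 0.80 = 28.8, which is 30 − 28.8 = 1.2 short.

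**Recruitment needed to keep the target at 20% dropout**, target / (1 − dropout):
- Total: 90 / 0.80 = 112.5, so 113.
- Per group: 30 / 0.80 = 37.5, so 38, which makes 3 × 38 = 114. This is also 19 whole blocks of 6.

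The gap between 108 and 113 or 114 is 5 or 6 participants, too large to be rounding.

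**Dropout that 108 can absorb while leaving 90:** 1 − 90/108 = 18/108 = 16.7%.

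**Effect on precision.** With a common SD, the normal-approximation 95% half-width for a difference between two group means, in SD units, is 1.96 × √(2/n):
- n = 30: 1.96 × √(2/30) = 0.51 SD.
- n = 28.8: 1.96 × √(2/28.8) = 0.52 SD.

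**Against the cited range.** 28.8 per group lies between 25 and 35.

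**The case against.** Several points on the other side are fair.

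- **The cause is not documented.** The protocol prints no formula. A 20% over-recruitment margin loosely labelled as dropout would give the same 108. This stands: multiplication by 1.2 is an inference from an exact match. It does not remove the mismatch, because the text calls the 20% dropout and nowhere defines it as a share of completers.
- **Measured is not defined.** Visits fall at baseline, 6 and 12 weeks, and the Interventions section keeps data from people who withdraw for the intention-to-treat analysis. Someone who leaves after week 6 still contributes post-baseline data. The shortfall therefore describes week-12 measurement or complete loss, and may overstate the data lost to the intention-to-treat analysis. The inconsistency remains, because the sentence itself treats dropouts as not measured.
- **The rationale does not rest on this sentence alone.** A reader might infer that the whole justification of the trial's size fails. The documents do not support that: the section also relies on the 25 to 35 per group range, which 28.8 still meets, and on a pragmatic balance of precision against resources.
- **No feasibility decision depends on the figure.** Because completion is a primary feasibility outcome, a reader might infer that a wrong dropout figure distorts how feasibility will be judged. The Primary feasibility outcomes section says only that numbers enrolling and completing will be measured. It sets no threshold, and nothing ties the 20% allowance to one.

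**Conclusion.** The inconsistency is real and minor. On the ordinary reading of dropout as a share of those recruited, 108 recruits at 20% loss leave about 86 measured (28.8 per group), not 90 (30 per group). The allowance that fits 108 and 90 is 16.7%.

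The size of the problem is about one participant per group and about 0.01 SD in the half-width of a two-group comparison, assuming a common SD and equal dropout across arms. The expected group size stays within the range that the protocol itself treats as adequate. The protocol makes no power claim, so none is affected, and the finding does not call for more participants.

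**What to change.** Keep 108 recruited and 36 per group, and reword the one sentence in Sample size in either of two ways:

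- 108 recruited allows for about 16.7% dropout, leaving 90 measured (30 per group); or
- 108 recruited with 20% dropout leaves about 86 measured (28 to 29 per group), within the cited 25 to 35 per group.

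The Allocation section then needs no change. The cost is one sentence and a slightly less favourable stated figure; recruitment, randomisation and analysis are unaffected.

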### Recruitment

We will recruit participants in several ways. People with metabolic syndrome who participated in a previous study in our School (the PATHWAY-27 study [28]), and consented to be contacted again for other research studies, will be contacted by phone or email to ask if they are interested in taking part in another intervention trial. We will also advertise the study broadly through conventional and social media and via multiple relevant charities (e.g. British Heart Foundation and Diabetes UK). We aim to achieve Health Research Authority approval, which will also permit recruitment through general practitioners’ offices. Based on experience with the PATHWAY-27 study [28], we anticipate recruitment and running of the trial to take 2 years. In the context of unforeseen risk events such as COVID19 or low recruitment rates, given our block design this time can be extended.

### Assignment of interventions

#### Allocation

While enrolment will be done by the study team, the randomisation schedule and allocation will be carried out by a collaborator who will not be involved in any other part of this trial and who will also be blinded to the dose allocation (Interventions ‘1’, ‘2’ or ‘3’; Fig. 1) designated by the manufacturer and provided in a sealed envelope. Randomisation and group allocation will be done based on predefined random allocation lists using simple stratification for sex (one each for males and females), with a block size of 6 and allocation list of 2:2:2; aiming to recruit 108 participants for *n* = 36 in each group.

#### Blinding

Both participants and researchers, including research team members and the collaborator, will be blinded to the dose allocation. The collaborator will maintain the dose allocation lists matching screening IDs to randomisation IDs, along with the manufacturer’s sealed envelope for the duration of the trial. This envelope will only be opened before study completion in the case of a serious adverse event. To test the success of blinding, 2 external questions will be added in the final visit of the health questionnaire—‘What dose of ergothioneine did you think you were taking during this period?’ & ‘Why?’.

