### Monitoring

The ErgMS trial management group will be comprised of the Chief ([name]) and lead investigators (XT, JS, JT) and will be responsible for the day-to-day running and management of the trial. As ergothioneine is an amino acid normally found in food and the doses of ergothioneine being tested (5 or 30 mg/day) are well below the safety limit (800 mg/kg bodyweight per day—e.g. a total of 56,000 mg/day for a 70 kg adult), the risk of harm or adverse event for adult participants with metabolic syndrome is considered low. Ergothioneine has minimal allergy risk determined by European Food Safety Authority [17]. Participants will be asked to inform the researcher if they feel unwell at any point during the study and their general health will be assessed through the health questionnaire at the 6- and 12-week visits.

Any participant reported adverse events will be recorded by the member of the trial management group in our adverse event reporting form and immediately report it to the Chief Investigator and assessed for causality. As necessary, the participant will be advised to consult their GP or relevant healthcare professional. In light of the relatively low risk study population with a noncritical indication (adults with metabolic syndrome), use of a food supplement with minimal risk, and short study duration, the ErgMS study does not have an independent data monitoring committee. In the unlikely event of a serious adverse event (SAE), the participant’s allocated intervention will be unblinded and the SAE and allocation will be reported to the Research Ethics Committee and the supplement manufacturer. Although there are minimal risks anticipated for this study, any adverse event or serious adverse event will be described according to its relatedness with the interventions, for both the total sample and by intervention arms, in the final study report.

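### The only code break described is one envelope with the key to all three arms, so unblinding one participant after an SAE exposes the whole code to whoever opens it

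*Protocol article*

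**What the plan says.** Three sections of the protocol article bear on this.

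- **Allocation.** Randomisation and allocation are done by "a collaborator who will not be involved in any other part of this trial". This person is "blinded to the dose allocation (Interventions ‘1’, ‘2’ or ‘3’; Fig. 1) designated by the manufacturer and provided in a sealed envelope". The coding is therefore by arm: three labels, one dose behind each.
- **Blinding.** "Both participants and researchers, including research team members and the collaborator, will be blinded to the dose allocation". The collaborator keeps the lists that match screening IDs to randomisation IDs, "along with the manufacturer’s sealed envelope for the duration of the trial". The trigger for a code break is then given: "This envelope will only be opened before study completion in the case of a serious adverse event".
- **Monitoring.** For a serious adverse event (SAE), this section states: "the participant’s allocated intervention will be unblinded and the SAE and allocation will be reported to the Research Ethics Committee and the supplement manufacturer". The wording is singular: one participant, one allocation.

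No participant-level code break is described. The recruitment target is 108, with 36 per arm.

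**The concern.** The device and its purpose do not match. Monitoring wants one participant's allocation. The only means the article gives is a key that translates all three intervention codes into doses. Whoever opens it to answer a question about one person learns what every code means.

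If the opener is the collaborator, that person then holds both the key and the lists, and is no longer blinded as the Blinding section says. If the affected participant's dose becomes known to staff who can also see intervention codes, everyone with the same code is decoded too.

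At stake is the blind for the visits and laboratory readings still to come. The trial is described as double-blind and checks the success of blinding at the last visit. A blind cannot be restored once it is lost. Recruitment and running are expected to take 2 years, so an early SAE could leave many participants still to be followed under an exposed code.

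**Working it through.** **1. Number of participants under the one key.** The Sample size section aims for 30 measured per group and allows 20% for dropout. 30 × 1.2 = 36 per arm, and 3 × 36 = 108. This reproduces the stated target.

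**2. The sections side by side.**

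| Point | Allocation and Blinding | Monitoring |
|---|---|---|
| Unit of the code break | One envelope, three arm codes | One participant's allocation |
| Trigger | An SAE | An SAE |
| Who is to remain blinded | Participants, research team, collaborator | Not addressed |
| Who is told | Not stated | Ethics committee and manufacturer |

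The trigger agrees. The scope does not. With an arm-level key, the result Monitoring asks for cannot be obtained without disclosing more than it asks for, at least to the opener.

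**3. How many allocations one opening could expose.**

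- With participant-level code breaks: 1 of 108.
- As written, if the opener passes on only one dose and staff cannot see intervention codes: that participant, plus whatever the opener now knows.
- As written, if one dose is passed on and staff can see the codes: one arm, 36 of 108.
- As written, for anyone who has both the opened key and the lists: up to 108 of 108.

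The article does not say which of the last three applies.

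**4. How likely an opening is.** The documents give no SAE rate and call the risk of harm low, so the rates here are assumptions.

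Maximum exposure is 108 × 12/52 = 24.9 person-years. With a Poisson count, P(at least one SAE) = 1 − exp(−rate × exposure). As a lower bound on exposure, counting only the 90 intended completers gives 90 × 12/52 = 20.8 person-years.

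| Assumed SAEs per 100 person-years | Expected number, 24.9 person-years | P(≥1), 108 participants | P(≥1), 90 completers only |
|---|---|---|---|
| 1 | 0.25 | 22% | 19% |
| 2 | 0.50 | 39% | 34% |
| 5 | 1.25 | 71% | 65% |
| 10 | 2.49 | 92% | 87% |

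A check with assumed per-participant risks, P = 1 − (1 − p)^108, gives 19% at p = 0.2%, 42% at 0.5%, 66% at 1%, 89% at 2% and 99.6% at 5%.

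The trigger as worded is not restricted to related events, so low toxicity of the supplement does not by itself make an opening unlikely. These figures are the chance that the envelope is opened. They do not measure the chance that an assessor or another participant learns a dose.

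**The case against.** A reader might infer that a single SAE breaks the blind for the whole trial. The documents do not support that.

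- The collaborator has no other role in the trial, and enrolment is done by the study team. The collaborator could open the envelope and release one dose only. The article states no route from the collaborator's knowledge to a biased measurement.
- Monitoring sends the allocation to the ethics committee and the manufacturer. The manufacturer designated the codes and already knows them. Nothing says that the key goes to staff, participants or the laboratory.
- Nothing says that staff see each participant's intervention code. The section on data management records only the randomisation number and date of birth on the data collection tools. Capsule labelling is not described in the text, and Fig. 1 is not available in the copy reviewed.

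A reader might also infer that causality is judged after unblinding. Monitoring mentions causality assessment before it turns to SAE unblinding and does not state the reverse order, so that inference is not supported either.

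It can further be said that code-break procedure is commonly left to the full protocol, and that this is a pilot whose primary outcomes are recruitment, completion and compliance, with many exploratory outcomes read by instrument or assay.

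Most of this stands, and it limits both the extent and the severity of the point. It does not remove it. The article names the device, its holder and its trigger, so the mismatch between an arm-level key and a one-participant intention lies in what is written, not in what was condensed away. Even the most careful handling ends the opener's blinding for all three arms.

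**Conclusion.** The point holds as a badly fixed mechanism. Followed as written, one SAE gives the opener the meaning of all three codes, although the stated intention is to unblind one participant. If the collaborator opens the envelope, the statement that this person is blinded is no longer true for the rest of the trial.

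The blind of up to 108 participants is put at risk, or of one arm of 36 if only one code is linked to a dose and staff can see the codes. The loss may be much smaller in practice. It depends on who opens the envelope, who is told and whether staff see the codes, none of which the article states. Whole-trial unblinding is the upper limit, not the expected result.

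The 22% to 92% chance of an opening rests entirely on the assumed rates of 1 to 10 per 100 person-years. No effect on any stated estimate has been shown. This should be fixed; confidence is moderate.

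**What to change.** Reconcile the Blinding and Monitoring sections so that the code break matches the one-participant intention:

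- Replace the arm-level key with participant-level code breaks, one per randomisation ID, so that one opening discloses one allocation.
- Label capsules with kit numbers that do not reveal the arm, in place of codes 1, 2 and 3.
- State who opens a code break and who is told, and keep the disclosed allocation from staff who assess outcomes.

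When unblinding is indicated stays with the investigators; this change does not touch it.

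The cost is a one-off labelling and code-list effort for about 108 IDs, by the manufacturer or the collaborator, and a minor amendment. The documents give no figure for this cost. The sample size, visits and analysis do not change.
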